**WHAT IS THE PRINCIPAL RESEARCH QUESTION/OBJECTIVE?**

**Main Hypothesis**

The main hypothesis to be tested is whether routine fixed dose oxygen treatment during the first 3 days after an acute stroke will reduce death and disability during the first 6 months after the stroke.

Stroke patients will only be included in to the study if the indication for oxygen is uncertain. Patients with definite indications or contraindications to oxygen will be treated according to established clinical practice.

It is possible that the proposed pilot study is too small to answer the research question, but it is necessary to inform the ensuing larger multi-centre study.

**The main objectives for the pilot trial are:**

To assess differences in death and disability (Rankin, Nottingham EADL and EuroQuol)at 6 months between the oxygen treatment and the control groups. This will be used to calculate the sample size for the planned multi-centre trial.

To assess potential side effects of oxygen treatment. These may include confusion and restlessness because of poor sleep, delayed return to mobility because of the physical restraint of the oxygen tubing and infections arising from oxygen insufflation.

To assess the frequency of protocol violation (oxygen given outside the trial protocol). This will further inform the sample size calculation for the multi-centre study.

To assess the feasibility of recruiting stroke patients within 24 hours of hospital admission. The recruitment rate will inform the number of centres required for a future multi-centre study of oxygen treatment.

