**Study size**

This is a pilot study and thus no formal study size calculation was undertaken since no estimate of effect size is available and the study is to be used to determine this as well as the feasibility of the planned multicentre study.

We plan to recruit 150 patients in each of the 2 trial arms. This would enable in the full sample detection of a small to medium effect size (0.4 SD of the main outcomes (Rankin, Nottingham EADL and EuroQuol) with 90% power and with a 5% two sided significance level. The study size was determined considering the following factors:

Ronning et al included almost 600 patients in their study of routine oxygen supplementation and did not find an overall difference on functional outcome at one year. There was a trend towards a better result with oxygen treatment in the 240 subjects with severe stroke, although this finding was not backed up by the use of a suitable test for heterogeneity. Our protocol may be more likely to show benefits because oxygen is given for longer, and titrated according to baseline oxygen saturation.[[46]](#endnote-47) However, given the data of the above study it is likely that any observed effect is small. This pilot study will provide us with data to inform a study size calculation.

Over the last year we performed a small study of the effects of oxygen supplementation for 24 hours within 3 days of admission on oxygen saturation. It showed a significant improvement of oxygen saturation in the treated group, but the study was not powered to look at functional outcomes. It took 6 months to recruit 50 patients for this study.[[47]](#endnote-48) It is therefore likely that we will be able to recruit 300 patients over three years.

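### The multicentre trial is to be sized from the treatment difference observed in this pilot, but with 150 per arm that difference is too imprecise to serve as the target if the effect is small, as the protocol expects.

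*Protocol*

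**What the plan says.** The first of the main objectives (Protocol, main objectives for the pilot trial) is to assess the 6-month difference in death and disability between oxygen and control. The next sentence reads: "This will be used to calculate the sample size for the planned multi-centre trial". The Study size section confirms that the effect itself is the quantity sought: "no estimate of effect size is available and the study is to be used to determine this". The Main outcomes section lists the efficacy comparisons under the label Effect size.

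On the size of the pilot, the protocol states: "We plan to recruit 150 patients in each of the 2 trial arms". It says this allows "detection of a small to medium effect size (0.4 SD of the main outcomes (Rankin, Nottingham EADL and EuroQuol". The operating characteristics attached to that claim are given as "with 90% power and with a 5% two sided significance level". The same section then comments on the earlier quasi-randomised oxygen study: "given the data of the above study it is likely that any observed effect is small". It puts no figure on small.

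The protocol-violation rate is named as a further input to the main-trial size, and the recruitment rate as the input for the number of centres. No smallest worthwhile difference, use of a confidence limit or other safeguard is given for the sizing step.

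**The concern.** Required sample size varies with the inverse square of the target difference, so an error in the target is magnified. An estimate 1.4 times too large halves the planned size, and one at 0.7 times the truth doubles it. A pilot of 300 estimates a treatment difference with a standard error that is about as large as a small effect. If that estimate becomes the target, a chance high value gives an underpowered multicentre trial, and a chance low value gives one far larger than needed. A zero or negative value gives no usable size at all. The protocol both expects a small effect and proposes to read that effect off the pilot, and these two statements do not sit well together.

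**Working it through.** **Inputs from the protocol.** 150 per arm; 90% power; two-sided 5%; 0.4 SD as the detectable effect. z values are 1.960 and 1.2816, sum 3.2416.

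**Assumptions, because the protocol gives no figure.** True effect 0.10 to 0.40 SD; risk of death or disability 30 to 50%; all 150 per arm evaluable; observed difference entered directly as the target for 90% power.

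**1. The plan's own figure.** n per arm = 2 × (3.2416/0.4)² = 131.3, so 132. With 150 per arm, power at 0.4 SD is Φ(0.4/0.1155 − 1.96) = 93.4%. The stated 90% is conservative and is not at issue. It describes what the pilot can detect, not how well it estimates a small effect.

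**2. Precision of the difference.**
- SE = √(2/150) = 0.1155 SD.
- 95% half-width = 1.96 × 0.1155 = 0.226 SD.
- Binary outcome: 1.96 × √(2p(1−p)/150) = 10.4 points at p = 0.30, 11.1 at 0.40 and 11.3 at 0.50.
- With an assumed 20% loss (120 per arm): 1.96 × √(2/120) = 0.253 SD.

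The half-width exceeds an effect of 0.10 or 0.20 SD. It is smaller than an effect of 0.30 or 0.40 SD.

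**3. What happens when the estimate is the target.** Let the estimate be d_obs, normal with mean d and SE 0.1155.
- Size needed: 2 × (3.2416/d)² per arm.
- Size planned: 2 × (3.2416/d_obs)² per arm.
- The planned size is within a factor of two only if d/√2 < d_obs < d√2. Zero and negative estimates count as outside.
- True power of a trial sized on d_obs > 0 is Φ(3.2416 × d/d_obs − 1.96). It is below 80% when d_obs > (3.2416/2.8016) × d = 1.157d.

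Example at d = 0.20. The factor-of-two limits lie (0.1414 − 0.20)/0.1155 = −0.507 and (0.2828 − 0.20)/0.1155 = 0.717 standard errors from the mean, so P(outside) = 1 − (0.763 − 0.306) = 54%. For power, (0.2314 − 0.20)/0.1155 = 0.272, with upper tail 0.393. Dividing by P(d_obs > 0) = 0.958 gives 41%.

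| Assumed true effect (SD) | Needed per arm | Estimate zero or negative | Size wrong by more than twofold | True power < 80%, given positive estimate | True power < 50%, given positive estimate | Median true power, given positive estimate |
|---|---|---|---|---|---|---|
| 0.10 | 2,102 | 19% | 76% | 55% | 35% | 72% |
| 0.20 | 526 | 4% | 54% | 41% | 13% | 88% |
| 0.30 | 234 | 0.5% | 36% | 34% | 4% | 90% |
| 0.40 | 132 | <0.1% | 23% | 29% | 1% | 90% |

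At a true 0.20 SD, the middle half of the sizes planned on a positive estimate runs from about 265 to 1,183 per arm, against 526 needed.

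**4. Contrast with a nuisance parameter.** For a roughly normal outcome, the relative SE of the pooled SD is about 1/√(2 × 298) = 0.041, so its 95% interval is about ±8%. Size varies with SD², so it moves by about −15% to +17% (0.92² = 0.846; 1.08² = 1.166). The pilot is well suited to supply this quantity.

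**The case against.** **Small is not quantified.** The only effect figure in the protocol is 0.4 SD. If the true effect were 0.3 to 0.4 SD, the median power of a trial sized on the estimate would be about 90%, and a twofold error would be the minority outcome. This stands, and it is why the result is shown across a range. However, 0.4 SD is given as the detectable effect, and the expectation stated separately is of a small one.

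**Direct entry of the point estimate is a reading of the text.** No formula is given, and the Study size section ends more softly, saying that the pilot will inform the calculation. It also lacks an SD, which the pilot would supply. This stands in part: the figures above describe the strictest reading. But the first objective says the difference will be used to calculate the size, Study size says the pilot is to determine the effect, and nothing in the protocol qualifies this.

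**The protocol already concedes that the pilot may be too small.** That caveat is about answering the research question. It leaves the sizing plan unchanged.

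**The consequence lies in another trial.** True. The conduct, data and analysis of this pilot are not made wrong, and the multicentre size will be fixed in its own protocol. The sizing use is nevertheless a stated objective here, so this is the place to correct it.

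**Two stronger readings a reader might infer.** One is that a chance low estimate would stop a worthwhile programme. The protocol has no stop or go rule tied to the estimate, and it refers to the multicentre trial as planned. The other is that the pilot as a whole would inform little but noise. Its objectives on side effects, protocol violations and recruitment, and its check of questionnaire completion, do not depend on the precision of the treatment difference.

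**Conclusion.** The point holds, limited to the use of the observed difference as the target for the main trial. At 0.10 to 0.20 SD, which is an assumed meaning of small, a planned size wrong by more than a factor of two is more likely than not (76% and 54%). At 0.30 and 0.40 SD it is less likely (36% and 23%), although 34% and 29% of trials sized on a positive estimate would still have true power below 80%. The figures rest on 150 evaluable per arm and on direct entry of the point estimate; loss to follow-up makes the precision worse. It would go too far to say that the main trial will be mis-sized whatever the true effect. The stated power of the pilot at 0.4 SD is not in question.

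**What to change.** Amend the first objective and the Study size section to say two things:

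- The pilot supplies the control-arm risk, SD, protocol-violation rate, follow-up rate and recruitment rate for the multicentre sample-size calculation. The violation and recruitment rates are already named as planning inputs, and questionnaire completion is already assessed.
- The target difference will be the smallest difference judged clinically worthwhile, set independently of the pilot's point estimate.

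Report the pilot difference with its 95% interval alongside the tests already planned, and use it only to check whether the target is compatible with that interval. The tests need not be removed.

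The cost is a few sentences. The pilot's size, conduct and patient burden do not change. The downside is that the sponsor must choose and justify a target difference.

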**Intervention**

Patients will be randomised to one of two treatment groups:

1. Treatment group 1: no routine oxygen supplementation during the first 3 days of randomisation.
2. Treatment group 2: oxygen per nasal cannula continuously (day and night) at a flow rate of 3l/min if baseline oxygen saturation is 93% or at a rate of 2l/min (if baseline oxygen saturation 93%) with humidification during the first 3 days after randomisation. Patients who develop definite indications or contraindications for oxygen treatment during the trial will be treated according to clinical need, irrespective of study treatment allocation.

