**Over night pulse oximetry and day 3 assessment**

In order to ascertain whether the prescribed oxygen supplementation effectively prevents hypoxia pulse oximetry will be performed over night on night two while the patient is receiving oxygen or control treatment. We will also be able to quantify the time the patients spend with an oxygen saturation above the normal range. This is necessary to fine tune the dosage schedule for the planned outcome study.

The day 3 assessment (Assessment Form 1) will document compliance with the trial treatment, relevant aspects of the patient's past medical history, and the stroke type (Oxfordshire Community Project Stroke Classification), and confirm completion of the over night pulse oximetry. If incomplete, pulse oximetry will be repeated on night 3 of treatment.

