**Main outcomes**

Comparisons will be made between the treatment and control group to determine:

1. Effect size:

- Death and disability (Rankin >3) at 6 months
- Scandinavian Stroke Scale week 1
- Mortality up to 6 months
- Rankin Score at 6 months
- Nottingham EADL score at 6 months

2. Potential Side effects of the study treatment

- Rate of infections (pyrexia or antibiotic treatment at week 1)
- Agitation (sedative or antipsychotic medication at week 1)
- Physiological indicators of stress (tachycardia, hypertension)

3. To assess the feasibility of the study protocol we will examine

- Protocol violations
- Recruitment rate
- The relation between the number of recruited and excluded patients
- The percentage of completed 6-month questionnaires

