**DATA ANALYSIS**

**Statistical analysis**

The main comparisons will be made between the control group and the treatment group.

The main analysis will be intention to treat, but a subgroup analysis excluding protocol violators will also be performed. Appropriate parametric and non parametric tests will be used to compare the groups at baseline and after treatment.

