**Stroke Oxygen Study**

# Day 3 Assessment (Assessment form 1)

Name Randomisation no

Pulse oximetry night 2 21:00-9:00 complete Yes No

If pulse oximnetry is not complete, repeat on night 3

Compliance with treatment regimen (tick the statement that applies on day 3)

| Oxygen currently in place (2) | Oxygen not in place, but patient and staff report that the patient is receiving oxygen (1) | No evidence of oxygen supplementation  (0) |
| --- | --- | --- |

Medical History (circle yes or no as appropriate)

| COAD or Asthma [by Hx or from list of drugs] | YES | NO |
| --- | --- | --- |
| Other chronic lung problem [kyphoscoliosis, thoracoplasty, pneumoconiosis etc) | YES | NO |
| Heart failure [by Hx or >20 mg frusemide or equivalent per day] | YES | NO |
| Ischaemic heart disease [H/O angina or MI or tx with nitrates or nicorandil] | YES | NO |
| Atrial fibrillation | YES | NO |

Stroke classification (circle the class that reflects the patient's worst symptoms)

| TAC | PAC | LAC | POC | TIA | Unclassifiable |
| --- | --- | --- | --- | --- | --- |

| Date of pulse oximetry |  |
| --- | --- |
| Baseline wake oxygen saturation |  |
| Mean nocturnal oxygen saturation |  |
| The 4% Oxygen Desaturation Index |  |
| The lowest nocturnal oxygen saturation |  |
| The time spent with an oxygen saturation <95% |  |
| The time spent with an oxygen saturation <92% |  |
| The time spent with an oxygen saturation <90% |  |
| The time spent with an oxygen saturation <80% |  |
| The time spent with an oxygen saturation >98% |  |
| The mean nocturnal heart rate |  |

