**Stroke Oxygen Study**

**Week 1 (Assessment form 2 a)**

Name Randomisation no

Date of death (if applicable)

Please complete the Notification of Death Form if the patient is deceased.

| Antibiotics prescribed since admission | YES | NO |
| --- | --- | --- |
| Continuous oxygen prescribed outside protocol for clinical indications | YES | NO |
| Sedatives or antipsychotic drugs prescribed since admission | YES | NO |
| Highest temperature during week 1 |  |  |
| **The highest heart rate during the 3 days of trial treatment** |  |  |
| **The highest systolic blood pressure during the 3 days of trial treatment** |  |  |
| **The highest diastolic blood pressure during the 3 days of trial treatment** |  |  |
| Highest temperature during week 1 |  |  |

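### Protocol violation is defined only as oxygen given outside the protocol, so allocated oxygen that was not received is missing from the departure rate meant to inform the multicentre sample size

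*Protocol*

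**What the plan says.** Under the main objectives for the pilot, the Protocol sets out "To assess the frequency of protocol violation (oxygen given outside the trial protocol"), and continues: "This will further inform the sample size calculation for the multi-centre study". The bracket is the only definition of the term in the document.

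The term is used twice more without being widened:

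- Main outcomes lists protocol violations under the lead-in "To assess the feasibility of the study protocol we will examine". Failure to receive allocated oxygen is not listed there.
- Statistical analysis makes intention to treat the main analysis and adds that "a subgroup analysis excluding protocol violators will also be performed".

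Two forms record oxygen use:

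- The day 3 assessment "will document compliance with the trial treatment". Assessment form 1 codes it 2 (oxygen in place), 1 (not in place but reported as being received) or 0 ("No evidence of oxygen supplementation"). The form is the same for both arms.
- Assessment form 2a at week 1 has a yes/no item: "Continuous oxygen prescribed outside protocol for clinical indications". It looks in the same direction as the definition in the objectives.

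The Intervention section says that patients who develop a definite indication or contraindication are "treated according to clinical need, irrespective of study treatment allocation".

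**The concern.** The violation rate has a stated purpose: to help size the next trial. Under intention to treat, a treatment contrast is diluted from two sides, by controls who receive oxygen and by oxygen-arm patients who do not. The definition can capture the first. It cannot capture the second, because a patient who received no oxygen was not given any outside the protocol. The document foresees non-receipt, since day-3 code 0 exists, but no section counts it as a violation, lists it as a feasibility outcome or connects it to the sample size.

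Two things are at stake. The planning rate taken from the pilot would be incomplete wherever it is used to correct a target effect for departures. And the analysis excluding violators would be cleaned unevenly between the arms, so it would not compare patients who received their allocated management.

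**Working it through.** **1. The definition applied by arm**

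| Patient | Violation under the main objectives? | In the analysis excluding violators? |
| --- | --- | --- |
| Control given oxygen outside the protocol | Yes | Removed |
| Control, day-3 code 0 | No (compliant) | Kept |
| Oxygen arm, day-3 code 2 or 1 | No | Kept |
| Oxygen arm, day-3 code 0 | No | Kept |

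The last row is the gap. Code 0 means opposite things in the two arms, so it is informative only when read by allocation.

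**2. The plan's own figures**

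The Protocol states no violation or compliance rate, so there is none to reproduce. Study size gives 150 per arm, 0.4 SD, 90% power and two-sided 5%. By the normal approximation:

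- 0.4 × √(150/2) = 3.464; 3.464 − 1.960 = 1.504; power = Φ(1.504) = 93.4%.
- 90% power needs 132 per arm.

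The stated 90% is therefore on the conservative side. Nothing below depends on it.

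**3. Dilution from each direction**

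Let c be the proportion of controls given oxygen and n the proportion of the oxygen arm not receiving it. Treating receipt as all or none:

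- observed effect = full-adherence effect × (1 − c − n);
- sample-size inflation = 1/(1 − c)² if only c is counted, and 1/(1 − c − n)² if both are.

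Both rates are assumptions. At c = 10%:

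| n | Inflation, c only | Inflation, both | Ratio |
| --- | --- | --- | --- |
| 10% | 1/0.90² = 1.23 | 1/0.80² = 1.56 | 1.27 |
| 20% | 1/0.90² = 1.23 | 1/0.70² = 2.04 | 1.65 |

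**4. Power if a full-adherence effect is corrected for c alone**

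For a trial sized at 90% power: power = Φ[(1.960 + 1.282) × (1 − c − n)/(1 − c) − 1.960].

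| c | n | (1 − c − n)/(1 − c) | Power |
| --- | --- | --- | --- |
| 5% | 10% | 0.895 | 83% |
| 5% | 20% | 0.789 | 73% |
| 15% | 10% | 0.882 | 82% |
| 15% | 20% | 0.765 | 70% |

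**5. When this applies**

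The first main objective says that the observed 6-month difference will be used to size the multicentre trial. An intention-to-treat difference already contains the factor (1 − c − n). Applying the inflation to it would count departures twice: at c = n = 10% the next trial would be oversized by 56% (1/0.80² = 1.56).

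The adjustment belongs only to a target effect set on a full-adherence scale. That route is realistic. With 150 per arm analysed, the 95% interval for a standardised difference is about ±1.96 × √(2/150) = ±0.23 SD, while Study size expects any effect to be small. The pilot difference may be too imprecise to serve as the target on its own.

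**The case against.** The strongest reply is that the harm depends on a sizing method the Protocol does not state. The next trial is to be sized from the pilot difference, which is already diluted from both sides, and the violation rate only adds to that. This stands, and it makes the power figures conditional. It does not remove the point, because the violation rate is named as a separate input and, as defined, is incomplete for that use.

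A second reply is that no data are lost: compliance and oxygen outside the protocol are both recorded, and the definition of violators for a secondary analysis could be left to the statistical analysis plan. The data are indeed there, which is why the fix is cheap. But the Protocol does not leave the term open. It defines it in a main objective and reuses it in the analysis section.

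A third reply is that code 0 is an imperfect measure of non-receipt. That is correct. It is one observation of a 72-hour treatment. Because of the clinical-need provision in the Intervention section, an oxygen-arm patient with code 0 may also have been managed as the Protocol allows. Code 0 should not be read as a violation in every case.

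A reader might infer that non-receipt is known to be substantial, since the background reports poorer compliance with masks. The document does not support that: the finding concerns masks, the trial uses nasal cannulae for that reason, and no cannula rate is given.

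**Conclusion.** The point holds as a defect of definition. Followed as written, the departure rate omits allocated oxygen not received, and the analysis excluding violators treats the arms asymmetrically.

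Its size is moderate and conditional. The 70-83% power range is an illustration that rests on assumed rates (c = 5-15%, n = 10-20%), all-or-none receipt, and a target effect on the full-adherence scale corrected for c alone.

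Two stronger conclusions are tempting and not supported:

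- That the multicentre trial will be underpowered. The Protocol does not say that it will be sized in the way the illustration assumes.
- That the exclusion analysis is biased towards no effect. Exclusion on events after randomisation selects patients. Controls given oxygen may be those who deteriorated, and removing them can shift the estimate either way.

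**What to change.** - **Main objectives and Main outcomes:** define departure from allocation in both directions and report by arm (a) oxygen given outside the protocol and (b) in the oxygen arm, allocated oxygen not received (day-3 code 0, read by allocation). Show separately the departures that follow a clinical indication or contraindication under the Intervention section.
- **Intervention and Assessment form 2a:** reconcile the two. The first allows treatment by clinical need in either arm; the second labels oxygen for clinical indications as outside protocol. Until they agree, rate (a) cannot be counted consistently.
- **Statistical analysis:** use the same two-directional definition for the analysis excluding violators, and label it supportive and open to selection bias. Intention to treat stays the main analysis.
- **Sample-size purpose:** state that both rates inform multicentre planning. An adjustment such as 1/(1 − c − n)² applies only when the target is a full-adherence effect, and not to the pilot's intention-to-treat difference.

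The cost is mainly wording, since the day-3 code is already collected in both arms. Showing clinically indicated stops separately means establishing the reason for each code 0, for which form 1 has no item. The departure rate will be larger and less favourable, and rate (b) will still rest on a single day-3 observation.
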